**Abstract of the Protocol**

|Study Design|□ Case-Control Study □ Cohort Study □ Cross-Sectional Study|
**☑**Randomized Controlled Trial (Blinding Applied) □ Other:|
|Study Type| (Category A: High Risk)|
|(Please select according to the project type)|□ Class III Clinical New Technology (Definite safety and efficacy, high technical difficulty and risk)|
|□ Special Population Study (Children, pregnant women, individuals with intellectual disabilities,

patients with mental disorders, etc.)|
|□ Off-Label Drug Study (□ Off-indication □ Off-route of administration □ Off-dose □ Off-age|
|□ Off-contraindication □ Off-population □ Other, please specify: )|
|□ Off-Label Device Study (□ Off-indication □ Off-use range □ Off-contraindication □ Off-population)|
|□ Other (Please specify: )|
|□ (Category B: Medium Risk)|
|□ Post-marketing Biologics Study (Preventive and therapeutic)|
|□ Post-marketing Therapeutic Vaccine Study|
|□ Post-marketing Orphan Drug Study|
|□ Class II Clinical New Technology (Definite safety and efficacy, certain technical difficulty, certain medical and ethical risks)|
|□ Other (Please specify: )|
|□ (Category C: Low Risk)|
|□ Post-marketing Drug Study (Including chemical drugs, generic drugs, etc.)|
|□ Post-marketing Device Study (Including AI, imaging software)|
|**☑**(Class I Clinical New Technology (Definite safety and efficacy, low technical difficulty, virtually no ethical risk in medical technology)|
|□ Other (Please specify: )|
|Total Number of Cases|486|
|Risk/Benefit Analysis|Adjusting blood flow rate affects filter lifespan without posing risks to patients|
|Risk Assessment|□ No greater than minimal risk (**☑**Greater than minimal risk)|
|Minimal risk: Refers to the possibility and extent of risks in the trial not exceeding those of daily life, or undergoing routine physical examination or psychological testing|

**I. Research Background**

Continuous renal replacement therapy (CRRT) is an effective treatment for acute kidney injury (AKI). Due to its continuous nature, mildness, and minimal impact on hemodynamics, it has been widely applied in clinical practice. The efficacy of CRRT is not only related to the treatment modality but also closely associated with the lifespan of the filter. A longer filter lifespan means fewer replacements and a lower risk of complications, thereby enhancing the safety and cost-effectiveness of the treatment.

Anticoagulation is a conventional practice in CRRT to prevent filter clotting and prolong filter lifespan. However, the use of anticoagulants carries a risk of bleeding, especially in patients with a tendency to bleed. Therefore, anticoagulant-free strategies have gained increasing attention, aiming to reduce anticoagulant-related complications while maintaining filter function and lifespan.

Blood flow rate is a critical operational parameter in CRRT, influencing both filter clotting risk and treatment efficacy. A higher blood flow rate can reduce the dwell time of blood in the filter, thereby lowering the risk of filter clotting and thrombus formation. However, for hemodynamically unstable patients, a higher flow rate may lead to decreased blood pressure and reduced cardiac output. An appropriate blood flow rate can ensure effective filtration and clearance of metabolic waste, thereby improving renal function. Thus, studying the impact of blood flow rate on filter lifespan in anticoagulant-free CRRT is of significant importance for optimizing treatment protocols, reducing medical resource consumption, and improving patient outcomes.

This study aims to investigate the impact of different blood flow rate settings on filter lifespan in anticoagulant-free CRRT, in order to provide more precise treatment parameters for clinical practice and improve the therapeutic outcomes for AKI patients.

**II. Research Objectives**

1. **Primary Objective:** To evaluate the impact of different extracorporeal blood flow rates on filter lifespan in CRRT without anticoagulation. By comparing filter lifespans under different blood flow rates, the optimal extracorporeal blood flow rate will be determined to maximize filter lifespan, reduce the number of filter replacements during CRRT, lower treatment costs, and improve patient outcomes.
2. **Secondary Objectives:**
   1. To explore the performance and efficacy of CRRT filters under different blood flow rates, including creatinine clearance, urea nitrogen clearance, and ultrafiltration rate.
   2. To analyze changes in hemodynamic parameters and physiological indices of patients under different blood flow rates, including arterial blood pressure, to assess the impact on patient physiological status.
   3. To study the impact of different blood flow rates on adverse events during CRRT, such as thrombus formation and bleeding complications, to evaluate safety and feasibility.
   4. To assess the clinical outcomes of CRRT treatment under different blood flow rates, including renal function recovery, survival rate, and hospital stay duration, to determine the optimal treatment strategy.

**III. Research Design, Methods, and Steps**

1. **Research Design**
   - **Study Type:** Single-center, single-blind, prospective randomized controlled trial (RCT)
   - **Randomization Method:** Each patient meeting the inclusion criteria will be randomly assigned to one of three groups (low blood flow rate group, medium blood flow rate group, or high blood flow rate group) by a study coordinator using a computer-generated random number table. Randomization will be conducted in a 1:1:1 ratio to ensure equal numbers of patients in each group, thereby maximizing the balance of patient characteristics and potential confounding factors across the groups. The study coordinator will not be involved in patient treatment or data collection and analysis. Group assignment information will be strictly confidential to ensure fairness. Each patient's randomization information will be recorded in a dedicated study database with appropriate security measures to prevent unauthorized access. All relevant researchers will receive training on the proper handling of randomization information. During patient selection and treatment, only authorized researchers will have access to group assignment information. These authorized personnel, including the principal investigator and the physician assigning treatment, will access the information through an encrypted electronic system to ensure data security and privacy. Unauthorized researchers will not have access to group assignment information to maintain the integrity of the single-blind design. All treatment and patient management decisions will be made by authorized personnel based on group assignment information and clinical conditions.
   - **Research Center:** West China Hospital, Sichuan University
   - **Sample Size Calculation:** The primary outcome measure of this study is filter lifespan. Therefore, filter consumption quantity is selected for sample size calculation. Based on retrospective and prospective cohort study data from our center, the smallest difference in filter lifespan was observed between the 200 mL/min and 250 mL/min blood flow rate groups. Thus, the maximum possible sample size can be calculated based on the lifespan difference between these two groups. Previous study results showed that the average filter lifespan was 28.09 ± 21.15 hours in the 200 mL/min blood flow rate group and 35.51 ± 17.97 hours in the 250 mL/min blood flow rate group. With a significance level (α) set at 0.05 and power at 0.90, the software PASS (Power Analysis and Sample Size Software) version 15 was used to calculate a sample size of N = 153 per group. Considering a dropout and refusal rate of 5%, the final number of filters required per group is at least 162, totaling at least 486 filters.
2. **Research Methods**

Patients undergoing CRRT at West China Hospital who meet the inclusion and exclusion criteria will be randomly divided into three groups: low blood flow rate group, medium blood flow rate group, and high blood flow rate group. The international standard blood flow rate for anticoagulant-free CRRT is 250 mL/min, while the standard blood flow rate for anticoagulant-free CRRT at our center is 200 mL/min. For hemodynamically unstable patients or those with high circuit pressure, our center reduces the blood flow rate to 150 mL/min based on experience, which is consistent with previous studies defining 150 mL/min as the low blood flow rate group [1]. Therefore, we define 150 mL/min, 200 mL/min, and 250 mL/min as the low, medium, and high blood flow rate groups, respectively.

- **Low Blood Flow Rate Group:** Adjust the CRRT blood flow rate to 150 mL/min.
- **Medium Blood Flow Rate Group:** Adjust the CRRT blood flow rate to 200 mL/min.
- **High Blood Flow Rate Group:** Adjust the CRRT blood flow rate to 250 mL/min.

The remaining CRRT prescription and parameter adjustments will be determined based on the patient's actual condition, experienced clinical physicians, and CRRT specialists. If during CRRT, high blood flow rate causes high vascular access pressure and requires a reduction in blood flow rate, the following principles will be followed:

- **Stepwise Reduction of Blood Flow Rate:** The blood flow rate will be reduced in increments of 50 mL/min, observing the patient's response and filter performance until a stable state is achieved.
- **Assessment and Recording:** After each adjustment, detailed records will be kept of the blood flow rate before and after adjustment, filter performance, patient's clinical manifestations, and reasons. Clinical judgment will be made based on the patient's actual condition to decide whether further adjustment is needed and to ensure patient safety and treatment efficacy. During data analysis, intention-to-treat analysis and per-protocol analysis will be used separately.
- **Record Filter Lifespan and Adverse Events:** Record the lifespan of the filters in the three groups, as well as the occurrence of clotting events and other negative events related to CRRT such as hypotension.

1. **Research Steps**

[Diagram]

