**VI. Detection Items and Time Points**

1. **Baseline Data:** At the time of patient admission, detailed records will be kept of demographic characteristics, laboratory indicators, examination results, primary disease, comorbidities, concomitant medications, blood pressure, etc.
2. **Filter Lifespan:** Each time a filter is replaced, the usage time of each filter will be recorded. Filters will be replaced based on the following criteria: obvious clotting in the filter, catheter, or venous chamber; filter usage time exceeding 72 hours (even if there are no other issues); patient needs to stop the machine for an outside examination or other treatments; treatment goals are achieved or CRRT is terminated.
3. **CRRT-Related Parameters:** After the CRRT prescription is established, detailed records will be kept of the CRRT prescription, including ultrafiltration rate, access, mode, etc. If the blood flow rate is reduced due to poor circuit performance or the anticoagulation method is adjusted due to coagulation function, the time, adjustment amount, and changes before and after adjustment will be recorded in detail.
4. **Filter Performance and Efficacy:** After CRRT is completed, the filter clearance performance will be recorded, including creatinine clearance, urea nitrogen clearance, cystatin C, and ultrafiltration rate.
5. **Patient Physiological Parameter Changes:** During CRRT, arterial blood pressure will be monitored every 2 hours, and the occurrence of hypotension and other hemodynamic instability events will be recorded.
6. **Adverse Events:** During CRRT, any adverse events that occur will be observed and recorded, including thrombus formation, bleeding complications, etc.
7. **Clinical Outcomes:** After CRRT is stopped, the patient's renal function recovery will be monitored, such as changes in creatinine and glomerular filtration rate. After discharge, the patient's survival status and hospital stay duration will be recorded.

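### Ultrafiltration rate is set and cut by clinicians who know the arm, so a difference between arms in the raw rate cannot be read as filter performance

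*Protocol*

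**What the plan says.** **Ultrafiltration as something clinicians set.** Section VI, item 3 makes it part of the prescription: "After the CRRT prescription is established, detailed records will be kept of the CRRT prescription, including ultrafiltration rate, access, mode, etc". Section III, Research Methods, lets the arm fix the blood flow at 150, 200 or 250 mL/min and leaves the rest to clinical judgement: "The remaining CRRT prescription and parameter adjustments will be determined based on the patient's actual condition, experienced clinical physicians, and CRRT specialists". Section VIII, in the item on managing adverse events, names a reduction in ultrafiltration as a response to hypotension.

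**Who decides, and what they know.** Section III, Randomization Method, gives the principal investigator and the physician assigning treatment access to the assignment. It closes: "All treatment and patient management decisions will be made by authorized personnel based on group assignment information and clinical conditions".

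**Ultrafiltration as an outcome.** Secondary objective 1 in section II is to explore how the filters perform at the different flow rates, "including creatinine clearance, urea nitrogen clearance, and ultrafiltration rate". Section VI, item 4 says that after CRRT "the filter clearance performance will be recorded, including creatinine clearance, urea nitrogen clearance, cystatin C, and ultrafiltration rate". Section XI, item 3 compares filter performance indicators between the arms by ANOVA.

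**What is logged.** For blood flow, section III asks for full detail: "After each adjustment, detailed records will be kept of the blood flow rate before and after adjustment, filter performance, patient's clinical manifestations, and reasons". Section VI, item 3 asks for the time and size of a change in these cases: "If the blood flow rate is reduced due to poor circuit performance or the anticoagulation method is adjusted due to coagulation function". Neither place names changes in ultrafiltration. Section VI, item 5 adds that "arterial blood pressure will be monitored every 2 hours, and the occurrence of hypotension and other hemodynamic instability events will be recorded".

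**The concern.** A performance measure should respond to the filter. Ultrafiltration rate responds first to the order that the clinician enters, and the clinician knows the arm. The protocol also supplies a route from arm to order that involves no bias by anyone. Section I says that a higher flow may lower blood pressure in hemodynamically unstable patients, and section VIII then has ultrafiltration reduced. Randomization does not remove this, because it arises after assignment.

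At stake is the interpretation of one secondary result. If the arms differ in raw ultrafiltration rate, the plan as written would place that difference under filter performance, although it may only show what was ordered.

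**Working it through.** The point rests on the text. The protocol states no figure for ultrafiltration that could be reproduced.

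**Step 1: the two roles side by side.**

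| Role | Where in the protocol |
|---|---|
| Prescribed by clinicians | Section VI, item 3; section III, Research Methods |
| Reduced for hypotension | Section VIII, management of adverse events |
| Filter performance measure | Section II, secondary objective 1; section VI, item 4 |
| Compared between arms | Section XI, item 3 (performance indicators as a class) |

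Section XI does not name ultrafiltration. Sections II and VI place it in the class that section XI tests.

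**Step 2: what the raw comparison measures.** Write P for the prescribed rate, r for the fraction delivered and D for the delivered rate, so that D = P × r. If the filters perform equally, r is the same in every arm, and the difference between two arms is ΔD = r × ΔP. The ANOVA on D tests whether the means of D are equal. It can therefore reject whenever ΔP is not zero, even with equal filters. The ratio D / P = r shows no difference in that case and does show one when delivery falls short of the order. Only the ratio separates the two explanations.

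**Step 3: can the planned records supply P and D?** Largely, yes. Section VI, item 3 records the prescribed rate and item 4 a value after CRRT. The detail not expressly required is the time, amount and reason of a later ultrafiltration change. Without it, P over the life of a filter is not fully known.

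**Step 4: size.** None can be derived, because the protocol gives no mean, SD or expected shift for ultrafiltration. The following is purely illustrative. Take three arms with n values each, one arm shifted by d SD and no filter effect. The noncentrality is n × (2/3) × d², with 2 and 3(n − 1) degrees of freedom. With n = 153 and d = 0.2 it is 153 × (2/3) × 0.04 = 4.08; the critical F(2, 456) is 3.015 and the ANOVA rejects in 42% of trials. At d = 0.05, 0.1 and 0.3 it rejects in 7%, 13% and 78%. With n = 76 the figures for d = 0.05, 0.1, 0.2 and 0.3 are 6%, 9%, 23% and 46%. The shifts are assumed. The 153 is a number of filters calculated for lifespan, not a planned number of ultrafiltration values. This is a generic power curve and says nothing about whether a shift will occur.

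**The case against.** **The comparison by arm is a proper randomized comparison.** A cut in ultrafiltration for hypotension caused by the flow is a consequence of the assigned arm, and the raw difference estimates that consequence. This stands. A reader might infer that the ANOVA is invalid or has an inflated type I error. For the effect of assigned flow under usual care it does not; only the reading as filter performance fails.

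**The sentence on decisions does not instruct staff to vary other care by arm.** A reader might infer a contradiction within section III, since the Randomization Method text covers all decisions and Research Methods ties only the flow to the arm. The sentence closes a paragraph about who may see the assignment, and setting the flow is itself a treatment decision. Research Methods then gives the operating rule. What remains is loose wording, and tightening it would not alone solve the ultrafiltration problem, because cuts for hypotension would continue.

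**The records are better than a quick reading suggests.** A reader might infer that cuts for hypotension go unrecorded. Section III separately asks for hypotension and other negative events to be recorded. Section VIII asks for the management of all adverse events whatever their severity, although the same section defines adverse events narrowly, as those that force CRRT to stop urgently or threaten life. Section VI, item 3 does not restrict the prescription record to the first prescription. So the gap is only that ultrafiltration changes are not among the changes for which time and amount are expressly logged.

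**Table layout and form fields can be left to an analysis plan or case report form.** That is fair for layout. The classification of a prescribed quantity as filter performance is made in the protocol, and an analysis plan cannot recover the timing of changes that were not collected.

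**Conclusion.** The point holds as a minor one. Ultrafiltration rate is both an order given by clinicians who know the arm and a measure that the protocol calls filter performance and compares between arms. A difference in the raw rate may reflect prescribing, including correct care for hypotension, and should not be reported as a property of the filter.

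The effect is confined to one measure under an exploratory secondary objective. Its size is unknown, and so is whether the arms will differ in prescribing at all. The conclusion assumes that ultrafiltration falls within the indicators tested in section XI, as sections II and VI indicate.

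A reader might go on to infer that the filter lifespan result is biased. The documents do not support that: performance bias is possible when clinicians know the arm, but nothing shows that it occurs or how large it would be, and the intention-to-treat analysis remains valid for assigned flow under usual care.

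**What to change.** 1. In section II and section VI, item 4, treat the prescribed ultrafiltration rate as a co-intervention and report it by arm. Use delivered relative to prescribed ultrafiltration, over the same period, as the performance measure. The raw delivered rate may still be shown by arm as an effect of assigned flow.
2. In section VI, item 3, add ultrafiltration changes to the existing log, with time, amount and reason.
3. As a small accompanying edit, reword the closing sentence of the Randomization Method text so that assignment is used only to set and manage the blood flow rate, with all other care following clinical condition as Research Methods already says.

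The cost is slightly more data entry, one additional table and one reworded sentence. No patients or staff are added, and clinicians stay free to change ultrafiltration when the patient needs it. The change makes prescribing that differs by arm visible; it does not prevent it.

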**IV. Case Selection**

1. **Inclusion Criteria**
   1. Patients undergoing CRRT;
   2. Age 18 years or older;
   3. No anticoagulant used during CRRT;
   4. Informed consent provided by the patient or their legal guardian/agent.
2. **Exclusion Criteria**
   1. Patients with severe coagulation disorders or undergoing anticoagulant therapy;
   2. Patients receiving intermittent renal replacement therapy (IRRT) or other non-CRRT treatments;
   3. Pregnant women.
3. **Criteria for Study Termination**
   1. **Safety Issues:** Serious adverse events: If during the study, the incidence of serious adverse events related to treatment such as hypotension, malignant arrhythmias, or death is significantly higher in one group compared to the other two groups, or exceeds the predefined safety threshold, consideration should be given to terminating that group's study. The safety threshold is set based on data from similar previous studies and the opinions of clinical experts to ensure patient safety. For example, if the incidence of bleeding events exceeds 10% and is 5% or more higher than the other groups; the incidence of thrombotic events exceeds 5% and is 3% or more higher than the other two groups; the incidence of infectious events exceeds 15% and is 5% or more higher than the other groups; the incidence of cardiovascular events exceeds 8% and is 4% or more higher than the other two groups [2,3].
   2. **Inadequate Effectiveness:** Interim analysis: Interim analysis will be conducted after 50% of the patients have been enrolled, performed by an independent statistician who is blinded to treatment allocation.
   3. **Interim Analysis Objectives:** To assess filter lifespan in different blood flow rate groups, compare filter blockage rates among groups, and evaluate the incidence of adverse events.
   4. **Interim Analysis Indicators:** Primary outcome measure: Filter lifespan (hours); Secondary outcome measures: Filter clotting rate, incidence of adverse events (bleeding, thrombus formation, etc.).
   5. **Interim Analysis Method:** Kaplan-Meier survival analysis will be used to assess filter lifespan, and the Log-rank test will be used to compare differences in filter lifespan among different groups. The chi-square test will be used to compare differences in filter blockage rates and adverse event incidence among groups.

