**XI. Statistical Analysis**

SPSS software (version 27.0, SPSS Inc., USA) and R version 4.2 (R Foundation for Statistical Computing, Vienna, Austria) will be used for data analysis.

1. **Descriptive Statistical Analysis:** Basic characteristics of the study sample will be described, including demographic features, laboratory indicators, underlying diseases, etc. Descriptive statistical analysis will also be conducted on filter lifespan, filter performance indicators, and changes in patient physiological parameters across different blood flow rate groups, including mean values, standard deviations, medians, etc.
2. **Survival Analysis:** Survival analysis methods (e.g., Kaplan-Meier curves) will be used to compare differences in filter lifespan among different blood flow rate groups. Cox proportional hazards models will be employed to analyze factors that may affect filter lifespan, such as blood flow rate, patient age, underlying diseases, etc.
3. **Analysis of Variance (ANOVA):** Differences in filter performance indicators among different blood flow rate groups will be analyzed using ANOVA.
4. **Safety and Adverse Event Analysis:** The incidence of adverse events (e.g., thrombus formation, bleeding complications) among different blood flow rate groups will be compared using chi-square tests or Fisher's exact tests to assess the safety of CRRT treatment at different blood flow rates.
5. **Clinical Outcome Analysis:** Appropriate statistical methods will be used to compare clinical outcomes, such as renal function recovery, survival rate, and hospital stay duration, among different blood flow rate groups.

A P-value of less than 0.05 will be considered statistically significant.

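### The 90% power at 153 filters per group is for a comparison of mean hours; the protocol plans only survival methods for filter lifespan, and for 200 v 250 mL/min a log-rank test would usually have less

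*Protocol*

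**What the plan says.** Protocol section III (Sample Size Calculation) takes filter lifespan as the primary outcome. It sizes the trial on the pair of groups with the smallest observed difference. For 200 mL/min it says "Previous study results showed that the average filter lifespan was 28.09 ± 21.15 hours"; the figure set against this is "35.51 ± 17.97 hours in the 250 mL/min blood flow rate group". It continues "With a significance level (α) set at 0.05 and power at 0.90", and PASS "was used to calculate a sample size of N = 153 per group". A 5% allowance for dropout and refusal raises this to 162 per group, 486 in all. The section gives no hazard ratio, event count or censoring share, and does not say which PASS procedure was used.

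Section XI (Survival Analysis) says "Survival analysis methods (e.g., Kaplan-Meier curves) will be used to compare differences in filter lifespan among different blood flow rate groups", and adds Cox models for factors that may affect lifespan, blood flow rate among them. ANOVA is reserved for filter performance indicators. Mean lifespan appears only among the descriptive statistics.

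Section IV names a test for the same outcome at the interim analysis: "the Log-rank test will be used to compare differences in filter lifespan among different groups".

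Section VI lists why a filter is replaced: clotting, "filter usage time exceeding 72 hours (even if there are no other issues", stopping for an examination or other treatment, and reaching the goal or end of CRRT. Usage time is recorded for every filter, whatever ended it.

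**The concern.** A stated power belongs to a particular test. A comparison of means uses the difference in hours and the SD. A log-rank or Cox comparison depends on the number of events and on how the hazard ratio behaves over time. The protocol states its power for the first kind of test and plans the second.

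The planning figures make this more than a formality. The 250 mL/min group has the longer mean and the smaller SD, so its advantage lies early and fades or reverses later. A log-rank test loses power in that pattern, and a single Cox hazard ratio would average opposite effects. Filters removed at 72 h or for reasons other than clotting may be censored, and a 5% dropout allowance does not address that.

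At stake is the contrast that fixed the sample size. If its real power were near 0.5, a true gain of 35.51 − 28.09 = 7.42 h would be missed about half the time.

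**Working it through.** **Inputs.** From section III: 28.09 (SD 21.15) and 35.51 (SD 17.97) hours, alpha 0.05 (sidedness not stated, two-sided assumed), power 0.90, 153 per group, 5% dropout. From section VI: the 72 h cap and the non-clot ends. The lifetime distribution and the share of non-clot ends are not given and are assumed below.

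**1. The plan's own figure.** SD² = (21.15² + 17.97²)/2 = 385.1, so SD = 19.62. Then n = 2(1.960 + 1.282)² × 385.1/7.42² = 147 per group; the exact t calculation gives 148. The rank-sum version multiplies by π/3: 147 × 1.047 = 154 and 148 × 1.047 = 155. At n = 153, t-test power is 0.909. Dropout: 153/0.95 = 161.05, rounded up to 162; 3 × 162 = 486. So 153 fits a comparison of hours.

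**2. It does not fit an event-based calculation.** With exponential lives, HR = 28.09/35.51 = 0.791. Schoenfeld events = 4(1.960 + 1.282)²/(ln 0.791)² = 765. Two groups of 153 hold 306 filters. With all 306 as events, power = Φ(√306/2 × 0.2344 − 1.960) = Φ(0.09) = 0.54. Exponential lives (CV 1) cannot match the stated SDs, so this is only a benchmark.

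**3. Shape of the hazards.** CV = 21.15/28.09 = 0.75 and 17.97/35.51 = 0.51. Weibull lives whose values after the 72 h cap match the stated moments have shape/scale 1.16/31.3 (200) and 1.96/40.6 (250). The hazard ratio for 250 v 200 is then 0.27 at 6 h, 0.82 at 24 h, 1.14 at 36 h and 1.97 at 72 h. Matched gamma and lognormal lives also cross between 24 and 36 h.

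**4. Simulated two-arm log-rank power, 200 v 250, 153 per group, two-sided 0.05** (1,500 to 5,000 replicates).

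| Lives matched to the stated means and SDs | Power |
|---|---|
| Weibull, matched after the 72 h cap | 0.45 to 0.48 |
| Weibull, matched before the cap, then capped | 0.71 to 0.72 |
| Gamma / lognormal, matched after the cap | 0.54 / 0.59 |
| No cap, every end an event: beta on 0–72 h / Weibull / gamma / lognormal | 0.39 / 0.65 / 0.70 / 0.85 |

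For 90% log-rank power the group size would be about 180 to 190 (lognormal, no cap), 300 (Weibull, no cap) or 350 to 450 (the shapes matched after the cap).

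**5. Non-clot ends.** Two readings of the planning hours are possible.
- *They include non-clot stops*, as recording every filter's usage time suggests. Keeping the hours and censoring a random 30% of ends gives about 0.35 to 0.57 for Weibull lives, and 0.41 (gamma) and 0.47 (lognormal) when matched after the cap.
- *They are times to clotting, with independent exponential censoring.* With about 40% to 57% of filters not clotting, Weibull lives give about 0.74 to 0.89. Observed use then averages well below the planned hours: about 20 v 25 h at 40%. This range is not a ceiling for other shapes. In a check with 3,000 replicates and censoring means of 50 h and 27 h, lognormal lives gave 0.85 to 0.93 and gamma lives (matched before the cap) 0.88 to 0.90.

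**6. Restricted mean to 72 h, Weibull lives, 153 per group.** Cap only: 0.90 to 0.96. Random 30% of ends censored at the planned hours: 0.61 to 0.73. About 41% independent censoring: 0.79 to 0.86.

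**7. All three groups.** The protocol gives no 150 mL/min figures. Assuming a mean of 28.09 − 7.42 = 20.67 h and the CV of the 200 group, three-arm log-rank power at 153 per group is about 1.00, and about 0.995 with 40% of ends relabelled as censored.

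**The case against.** The strongest reply is that the final test is not fixed. Log-rank is named only for the interim analysis; section XI gives Kaplan-Meier curves as an example, and Cox is there to examine factors. The exact test and a proportional-hazards check commonly belong in a statistical analysis plan, which may exist. This stands, and a reader should not infer that the protocol commits its final comparison to log-rank. It does not remove the mismatch: the protocol states a power, plans no test of mean lifespan, and the methods it names (log-rank, Cox) are hazard-based.

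A reader might also infer that the trial as a whole is underpowered. The documents do not support that. Lifespan is compared among three groups, and step 7 shows that the overall test could be very well powered if 150 mL/min lies at least as far away. The shortfall concerns 200 v 250.

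Nor do the documents support a single figure for the shortfall, or the idea that a hazard-based test must fall below 0.90. Lognormal lives at 162 per group with the cap applied after matching reach about 0.90, though with no dropout or other censoring and with observed moments that no longer equal the plan's. Some shapes in step 5 reach it too. Whether censoring lowers or raises log-rank power depends on which reading of the planning hours is taken, so no general trade-off against restricted mean can be drawn.

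Finally, restricted mean is partly a preference. An early-weighted Peto-Peto test, also a survival method, gave 0.97 to 0.99 in the uncensored two-arm scenarios.

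**Conclusion.** The point holds in limited form and should be fixed. The 90% at 153 per group belongs to a comparison of fully observed hours, and the protocol plans no such comparison. On the plan's own means and SDs, log-rank power for 200 v 250 at 153 per group is about 0.45 to 0.72 for Weibull lives with the cap, and about 0.39 to 0.85 over the other matched shapes. With non-clot stops, Weibull lives give about 0.35 to 0.57 on one reading of the planning hours and 0.74 to 0.89 on the other.

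The mismatch itself needs no assumption beyond the text. Its size rests on assumed lifetime shapes and censoring shares, a two-sided test, and one filter per independent unit. Multiplicity over three groups and the interim look are not included.

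**What to change.** Name the primary test for filter lifespan, and say which ends count as events and which are censored. Restate the power for that test on the 200 v 250 contrast, using the lifetime distribution and the share of filters ending in clotting from the centre's own cohort. The protocol should not claim 90% for a hazard-based test unless that calculation supports it.

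One option keeps the planning quantity: make the difference in restricted mean filter life to 72 h the primary comparison, with log-rank and Cox as supportive analyses and a proportional-hazards check. An early-weighted survival test is an alternative.

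The cost is a wording change and one recalculation from data that the centre holds, made before any comparative results are seen. The stated power will probably become less favourable. Which test does better depends on how non-clot stops are handled, so that decision comes first.
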